### Patient-level outcomes

The co-primary patient mental and physical outcomes are (1) PHQ-9 response at 6 months, defined as at least a 50% improvement in PHQ-9 score compared with baseline; and (2) viral load suppression 12 months after patient enrolment, defined as a viral load value of < 1000 copies/mL in line with the third ‘90-90-90’ target [1].

There are multiple ways of managing the participant level analysis metric for the PHQ-9, which we are using both to define eligibility in this trial (score of 9 or more) and to assess response to treatments. We have selected as the primary outcome measure the response at 6 months, defined as a 50% improvement from baseline score. Secondary outcome measures related to PHQ-9 include response at 12 months; mean scores at 6 and 12 months; remission, defined as a score of 5 or less at 12 months; and category of severity (mild, moderate, severe) at 6 and 12 months. We record the treatment for depression, including initiation or intensification of antidepressant medication, referral to a counsellor for depression counselling, number of contacts with a counsellor, and referral to a mental health specialist (clinical psychologist, psychiatrist or secondary care services). The Perceived Stress Scale is included to measure the degree to which life situations are considered stressful [59].

Secondary HIV measures are viral suppression at 12 months defined as a viral load of < 400 copies/mL, virologic failure defined as two consecutive viral load values > 1000 copies/mL, and change in viral load values over time. Other ART-linked outcomes include programme retention, appropriate maintenance on enrolment ART regimen and ART regimen switched to second line, and the Internalised AIDS Related Stigma Scale [60], which we include to explore the relationships between stigma, retention in care and viral load suppression.

Viral loads will be measured using venous samples in participants at baseline and at the 12-month follow-up interview, and the samples submitted to the National Health Laboratory Service responsible for routine viral load monitoring, which current ART programme guidelines recommend should occur annually [61]. Thus, the majority of patients are expected to undergo both routine programme and research viral load monitoring during the course of the trial. Funds available for viral load monitoring as part of the trial are limited and therefore only patients with no documented programme results (in the past 6 months) will be asked to submit a baseline research viral load. Research-funded 12-month viral loads will be collected on all patients as this is the primary physical outcome.

We will also aim to collate all programme and research-viral loads into a single longitudinal record for every patient enrolled in the trial, through linkage with the viral load repository at the National Health Laboratory Service and application of algorithms for this linkage previously applied to province-wide ART datasets [27]. In South Africa, detectable viremia is most commonly caused by non-adherence, and only rarely due to resistant virus [62]. Thus, the proportion of participants with a suppressed viral load provides a reasonable estimate of ART adherence. In addition, we have included a Visual Analogue Scale for self-reported adherence in the last month as a secondary outcome measure at 12 months [63–65]. The integrated care nature of the intervention, with a focus on the detection and management of chronic diseases, and the surge in multi-morbidity in the general population, and ART populations in particular [66], are the reasons for monitoring risk factors for cardiovascular diseases (blood pressure, weight, smoking status) and the detection and treatment of other chronic diseases.

We will assess the provision of integrated care from a patient perspective using the Patient Assessment of Care for Chronic Conditions [67] at 12 months. Economic outcomes include healthcare utilisation, productivity and the World Health Organization’s Disability Assessment Scale [68]. We will monitor potential harms, including hospitalisation, death and suicide, the last two through follow-up at clinics, linkage with the national mortality register, and interviews with clinic staff and family members. Table 4 provides a full list of outcomes, time of measurement and source of data. In the section on ‘Adverse events and monitoring of possible harms’ and in Table 5, we describe in more detail outcomes reflecting possible harms and methods used for their detection.

**Table 4 Tab4:** Schema of patient-level data collection

Outcome						
				Baseline	6 months	12 months
Outcome	Measurement	Source	Metric			
Primary measurements						
Depression symptoms	PHQ-9	Self-reported	50% reduction in PHQ-9 score	●^1^	●●^2^	●
Viral load suppression	Viral load value	Research- and programme-funded viral loads (latter through documentation during interviews and linkage to routine databases)	Viral load <1000 copies/ml	●	●	●●
Secondary mental health outcomes						
Depression symptoms	PHQ-9	Self- reported	50% reduction in PHQ-9 score	●	●	●●
Depression symptoms	PHQ-9	Self- reported	Remission defined as score of <5 on PHQ-9	●	●	●●
Depression symptoms	PHQ-9	Self- reported	Mean PHQ-9 scores at 6 and 12 months	●	●●	●●
Depression symptoms	PHQ-9	Self- reported	Category of depression: proportion with mild, moderate or severe depression	●	●●	●●
Antidepressant treatment		Self- reported	Proportion with antidepressant treatment initiated or intensified	●	●	●●
Counselling		Self- reported	Proportion receiving counselling by clinic-based counsellor	●	●	●●
Referral to specialist mental health worker/ service		Self- reported	Proportion referred	●	●	●●
Stress	Perceived Stress Scale	Self-reported	Difference in means	●		●●
Secondary HIV measurements						
Viral load suppression	Viral load value	Research- and programme-funded viral loads	Viral load <400 copies/ml	●	●	●●
Virologic failure	Viral load values	Research- and programme-funded viral loads	Two consecutive viral load values >1000 copies/ml	●	●	●●
Change in viral load values over time	Viral load values	Research- and programme-funded viral loads	At least half a log difference between viral load values, unless there are two viral loads >2000 copies/ml	●	●	●●
ART treatment	ART regimen	Self-report	Clinically appropriate switches to second line ART therapy	●		●●
ART adherence	Visual Analogue Scale	Self-report	Difference in means	●		●●
Stigma	Internalised AIDS-Related Stigma Scale	Self-report	Difference in means	●		●●
Integrated care outcomes						
Cardiovascular risk factors	blood pressure, weight, body mass index, waist circumference	Interviewer measured	Difference in means	●	●	●●
Diagnosis of other comorbid illnesses		Self-reported	Proportion diagnosed	●		●●
Disability	WHO Disability Assessment Schedule 2.0	Self- reported	Difference in means	●		●●
Quality of chronic illness care received	Patient Assessment of Care for Chronic Conditions (PACIC)	Self-reported	Mean PACIC score	●		●●
Retention in care		Self-reported; clinic records	Proportion in care	●		●●
Health economic outcomes						
Healthcare utilization		Self- reported; linkage with hospitalisation databases	Incidence rate ratio	●		●●
Productivity and economic outcomes		Self- reported		●		●●
Safety measurements						
Hospitalisation		Self- reported; linkage with hospitalisation databases	Proportion hospitalised	●	●	●●
All-cause mortality		Clinic, report, linkage with mortality register	Proportion died	●	●	●●
Suicide		Follow-up of cause of all known deaths with clinic and family interview	Proportion suicides	●	●	●●

^1^● data measured

^2^●● time when endpoint for outcome will be reported

**Table 5 Tab5:** Defining, monitoring and reporting of harm

Type of harm	Source and method of identification	Action(s) to mitigate harm to specific participants	Reporting frequency and to whom
*Adverse Events*			
Positive response to ninth item of the PHQ-9: “Thoughts that you would be better off dead or of hurting yourself in some way”	Participant interviews (baseline, 6-month follow-up, 12-month follow-up)Flag within electronic questionnaire prompting interviewer to act	Repeat question to reduce telescoping-type reporting errorsIf ≥ 8 days in last 2 weeks, immediate referral to clinic staffIf between 1 and 7 days, then written educational material given	6 monthly report to DSMB6 monthly to IRB (with DSMB letter of recommendation)
PHQ-9 score of ≥ 20 at 12 months suggesting persistent severe depression	Participant interviews (12-month follow-up)Data report (monthly)	Summary forwarded to clinic together with recommendations for further treatment	6 monthly report to DSMB6 monthly to IRB (with DSMB letter of recommendation)
Blood pressure severely raised (≥ 180/110) placing participant at immediate risk of cardiovascular event	Participant interviews (baseline, 6-month follow-up, 12-month follow-up)Flag within electronic questionnaire prompting interviewer to act	Immediate referral to clinic staff for review	6 monthly report to DSMB6 monthly to IRB (with DSMB letter of recommendation)
Raised blood pressure at follow-up representing undiagnosed or uncontrolled hypertension	Participant interviews (baseline, 6-month follow-up, 12-month follow-up)Longitudinal patient record	Summary forwarded to clinic together with recommendations for further treatment	6 monthly report to DSMB6 monthly to IRB (with DSMB letter of recommendation)
Detectable viral load at follow-up representing possible adherence problems or treatment failure	Participant interviews (baseline, 6-month follow-up, 12-month follow-up)Research viral loadsRoutinely collected viral loadsLongitudinal patient record	Summary forwarded to clinic together with recommendations for further treatment	6 monthly report to DSMB6 monthly to IRB (with DSMB letter of recommendation)
*Serious Adverse Events*			
Significantly raised viral load (> 1000 copies/mL) during pregnancy placing fetus at risk of HIV transmission	Participant interviews (baseline, 6-month follow-up, 12-month follow-up)Research viral loadsRoutinely collected viral loadsData report (weekly)	Immediate notification of PI (LF) or delegate (NF) who will personally call clinic and follow-up with them until we can be sure woman is back in care and appropriately treated	Notification of IRB, DSMB and NIMH within 7 days of knowledge of confirmation
Hospitalisation	Participant interviews (baseline, 6-month follow-up, 12-month follow-up)Routinely collected hospitalisation dataData report (monthly)	No immediate action other than 6 monthly review by DSMB	6 monthly report to DSMB6 monthly to IRB (with DSMB letter of recommendation)
Death (excluding suicide)	Participant interviews (loss to follow-up form)National population registerData report (monthly)	No immediate action other than 6 monthly review by DSMB	6 monthly report to DSMB6 monthly to IRB (with DSMB letter of recommendation)
Death by suicide	Participant interviews (loss to follow-up form)National population register (provided we are able to access cause of death)Data report (weekly)	Immediate notification of PI (LF), who will follow-up with fieldwork staff to confirm suicide and establish date of suicide	Notification of IRB, DSMB and NIMH within 7 days of knowledge of confirmed suicide

*DSMB* Data and Safety Monitoring Board, *IRB* Institutional Review Board, *NIMH* National Institute of Mental Health, *PI* principal investigator

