### Objectives

The primary objective of the CobALT trial is to compare the effectiveness of a scalable intervention for collaborative care of depression by non-specialist mental health workers with usual services on the mental and physical outcomes in adults on lifelong ART with comorbid depression. The two primary hypotheses are that the intervention will (1) reduce depressive symptoms at 6 months and (2) improve viral load suppression status at 12 months. Secondary objectives are (1) to assess the effect of the intervention on the provision of integrated care for chronic illnesses in the intervention facilities from the perspective of service managers and providers as well as service users and (2) to evaluate the cost effectiveness of the intervention.

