### Sample size

We calculated the sample size for a superiority trial because we hypothesized that the intervention would lead to reduced depressive symptoms for patients on ART with comorbid depression, which would in turn positively influence their adherence to ART and care, and improve their HIV outcomes. We based our estimates of viral load suppression on data from our previous RCT on task-shifting HIV care in which 70% of ART patients had suppressed viral loads at follow-up with an intra-clinic correlation coefficient (ICC) of 0.046 [40]. We assumed that rates of viral load suppression will be slightly lower in a group of patients suffering from depression (65%) as it is a known risk factor for poor adherence [18, 70]. A sample size of 2000 participants from 40 clinics (50 patients per clinic, 1000 per group) provides 80% power to detect a 10% difference in 1-year viral load suppression at the 5% significance level assuming an ICC of 0.04 and a 20% loss to follow-up based on a previous trial in this setting [38]. To determine the appropriate parameters for the PHQ-9 sample size calculation we searched PubMed for all RCTs which had used the PHQ-9 as an outcome. Of the 126 trials screened, we identified nine as relevant to the design of our trial [71–79], including four cluster trials and five individually randomised studies. The trials used a mix of metrics, including difference in means, response and remission rates, measured at a range of time points. We disregarded several of the trials because their baseline scores were far higher than those we had observed in our population of interest during the validation of the Setswana localisation of the PHQ-9. We instead based our sample size estimates on three cluster trials completed in the Netherlands [71], Italy [77] and the UK [79], where PHQ-9 response rates at 6 months were reported and where baseline scores were similar to what we anticipated. Only two of the five cluster trials reported an ICC [71, 79] and, in one of these, it was uninterpretable because of very small cluster sizes [71]. We then completed a series of calculations to determine power to detect a difference of between 10% and 12% in response rates at 6 months, with the number of clusters and cluster size fixed by the viral load calculation at 40 and 50, respectively (Table 6). We allowed for the proportion of those who responded in the control group to vary between 30% and 35%, for the ICC to vary between 0.02 and 0.04 (we assumed lower ICCs were likely given that the PHQ-9 is a health outcome) and for a loss to follow-up rate of 20%. This showed that a sample of 50 patients in 40 clusters (1000 per group) yielded a power of between 73% and 96% to detect a difference of between 10% and 12% in response rates at 6 months.

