### Statistical methods

We will estimate the effects of the intervention by comparing the outcomes of intervention and control group patients using multiple mixed effects regression models, with clinics as a random effect to account for the intra-cluster correlation of outcomes. We will include the stratum as a covariate in the regression models, and will use Stata statistical software for the analysis. All clinics and patients will be analysed in the treatment group to which they were randomly assigned. We will ascertain the completeness of follow-up by group to evaluate the integrity of the planned analysis. We will use binomial regression to estimate differences in proportions of patients with suppressed viral loads and who have responded in terms of their depressive symptoms, measured using the PHQ-9. We will analyse secondary outcomes as follows: binomial regression for binary outcomes, linear regression for changes in depression scores, blood pressure, weight, and waist circumference by comparing values at follow-up adjusted for baseline values, and Poisson regression for count outcomes such as clinic visits and inpatient days, accounting for individuals’ duration of follow-up.

Planned secondary analyses include analysis of primary outcomes stratified and adjusted for treatment severity, treatment status and comorbidities at baseline. We will also explore whether there is a differential effect among those patients who reported receiving the counselling intervention.

The economic evaluation will include descriptive statistics describing the health system and societal costs of living with HIV and depression, a cost effectiveness analysis, and modelling of the intervention beyond the timeframe of the study.

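### The secondary outcome for change in viral load (Table 4) has no direction and an ambiguous exception, so its result cannot be read as benefit or harm

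*Protocol article*

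**What the plan says.** The section Patient-level outcomes lists "change in viral load values over time" among the secondary HIV measures and adds nothing about how it is scored. Table 4 supplies the metric: "At least half a log difference between viral load values, unless there are two viral loads >2000 copies/ml". The table marks 12 months as the reporting time and names research- and programme-funded viral loads as the source.

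The other viral load outcomes all have a clear direction: below 1000 copies/mL (co-primary), below 400 copies/mL (secondary), and "virologic failure defined as two consecutive viral load values > 1000 copies/mL". The second hypothesis under Objectives is directional too: the intervention will "improve viral load suppression status at 12 months".

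Statistical methods assigns "binomial regression for binary outcomes". Its list of outcomes for linear regression adjusted for baseline names depression scores, blood pressure, weight and waist circumference, but not viral load. A yes/no half-log metric therefore falls under the binomial rule.

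**The concern.** A difference of at least half a log has a size but no sign. A patient whose viral load falls tenfold and one whose load rises tenfold both meet it. An effective intervention should produce more falls and fewer rises, and an unsigned count adds the two together. The between-arm contrast then depends on the route by which the benefit arises and not only on how large it is.

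The exception makes this worse. The word introducing it does not say whether patients with two values above 2000 are left out, scored as no change, or scored as changed regardless. The article does not explain the cut-off either. Whether a patient falls under the exception depends on viral loads taken during follow-up, which the intervention is meant to alter. The intervention could therefore change who is affected by it.

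At stake is whether a published result for this outcome, null or not, says anything about benefit or harm.

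**Working it through.** **1. Inputs.** From Sample size: 65% suppressed in control, a 10-point effect (so 75% in intervention), 20 clinics of 50 patients per arm, ICC 0.04, 20% loss. The article gives no figures for the shares of patients who rise or fall. Those used below are assumptions.

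**2. The plan's own figure.** The article states no power for this secondary outcome. For suppression it says the sample "provides 80% power to detect a 10% difference in 1-year viral load suppression at the 5% significance level". The ICC and the loss behind that figure are the ones listed in step 1. With 50 × 0.8 = 40 patients per clinic, the design effect is 1 + 39 × 0.04 = 2.56 and the effective size per arm is 20 × 40 / 2.56 = 312.5. Power for 65% against 75% (two-sided 5%) is then 78.0%. With no loss, the design effect is 1 + 49 × 0.04 = 2.96, the effective size is 337.8 and power is 81.1%. This is close enough to the stated 80% to confirm that the inputs are read correctly.

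**3. The unsigned count.** Assume that both arms start at 65% suppressed and that control stays there, so rises equal falls. Assume also that every crossing of the threshold is at least half a log, that there are no other half-log changes, and that nobody meets the exception. Let f be the share of the 10-point gain that comes from more falls, the rest coming from fewer rises.

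- Falls, intervention = falls, control + 10f
- Rises, intervention = rises, control - 10(1 - f)
- Difference in the unsigned count = 10f - 10(1 - f) = 10(2f - 1) points

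With 10% rising and 10% falling in control (unsigned count 20%):

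| Share of gain from falls (f) | Falls, intervention | Rises, intervention | Unsigned count | Difference from control | True gain in suppression |
|---|---|---|---|---|---|
| 1 | 20% | 10% | 30% | +10 | 10 |
| 0.75 | 17.5% | 7.5% | 25% | +5 | 10 |
| 0.5 | 15% | 5% | 20% | 0 | 10 |
| 0.25 | 12.5% | 2.5% | 15% | -5 | 10 |
| 0 | 10% | 0% | 10% | -10 | 10 |

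With the effective size of 312.5 per arm (ICC of 0.04 carried over), power to declare a difference is 82.5% in the first row and 94% in the last. The same benefit could thus be statistically significant with either sign.

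**4. How far this depends on the assumed movement.** Rises cannot go below zero, so the rises in control must be at least 10(1 - f) points. An even split is possible with 5%, 6.5% or 10% of control patients moving each way, and gives exactly 0 in each case. At 6.5%, for example, intervention has 11.5% falls and 1.5% rises, which sum to 13.0% as in control. A negative difference needs more than 5% of control patients to rise. With 3% each way, f must be at least 0.7 and the difference stays at or above 10(2 × 0.7 - 1) = +4.

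**5. Directional outcomes on the same inputs.** The difference in falls is 10f, never negative. The difference in rises is -10(1 - f), never positive. Falls minus rises is 10f + 10(1 - f) = 10 for every f, which is the suppression gain. At the even split, falls are 15% against 10% and rises 5% against 10%.

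**6. The exception and the suppressed range.**

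- 100,000 to 3,000: log10(3,000/100,000) = -1.52; both values above 2000.
- 50,000 to 2,100: -1.38; both above 2000.
- 3,000 to 100,000: +1.52; both above 2000.
- 50 to 200: +0.60; counts as change although both values are below 400.

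On the natural reading, the first three patients leave the half-log rule and the fourth stays in it.

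**The case against.** Table 4 never says that rises and falls are pooled; it is silent on direction. It is one cell in a condensed article, and a statistical analysis plan that is not shown may fix the direction, the pair of values compared and the handling of the exception. This stands to the extent that a reader should not say the investigators chose a two-way count. It does not remove the point. The article states a metric, and that metric applied as worded is unsigned, while every neighbouring viral load outcome carries its direction.

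A reader might infer that rises and falls will cancel and the outcome will show nothing. The documents do not support that. Exact cancellation needs an even split, the movement shares are assumed, and if most of the benefit came through falls the unsigned count would still move with it.

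A reader might also infer that patients with two values above 2000 are definitely set aside. That is the natural reading, but the clause could mean that they count regardless. Under that reading persistent viraemia, rises and falls would share one category, which is no easier to interpret. A patient who goes from 100,000 to 3,000 is still unsuppressed on both of the trial's cut-offs, so withholding credit is not absurd in itself. The 2000 cut-off is unexplained, which does not make it wrong.

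Finally, this is one secondary row in a long table. The directional viral load outcomes remain readable, and the collated longitudinal record allows rises and falls to be separated at analysis.

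**Conclusion.** The point holds for this secondary outcome. As worded, the metric counts improvement and deterioration alike, so its between-arm difference carries no reliable sign. For a true 10-point gain in suppression it ranges from +10 to -10 points if 10% of control patients move each way. The range is narrower if fewer move, and zero is out of reach if fewer than 5% of control patients rise. These figures rest on the assumptions in step 3 of the working. The loss of sign does not depend on them, nor on how the exception is read.

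The exception is a second, separate weakness: it is ambiguous, it uses a cut-off found nowhere else in the article, and it depends on follow-up values. Nothing here touches the co-primary outcome of suppression below 1000 copies/mL at 12 months, the sample size, or the other viral load outcomes. The definition should be corrected, but the trial's main conclusions do not depend on it.

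**What to change.** Replace the Table 4 metric with two separate binary outcomes: a fall of at least 0.5 log10, and a rise of at least 0.5 log10. Take each from the baseline value (the recent programme result or, where there is none, the baseline research sample) to the 12-month research sample. Analyse both with the binomial model already planned, and report them side by side.

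Drop the exception for two values above 2000. Any two consecutive values above 2000 are also above 1000, so that form of persistent viraemia is already captured by the virologic failure outcome.

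A signed change in log10 viral load, adjusted for baseline, could be added, but only with a method that treats values below the assay limit as censored. With about 65% of patients assumed suppressed, many values may lie at or near that limit, and the article does not state what it is.

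The cost is one line in the outcome table and the matching line in the analysis plan. Baseline and 12-month viral loads are already being collected, so no new data are needed. Trial status reports follow-up still in progress in one district, so the change can be recorded before the final analysis.
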